### Statistical Analysis

To statistically analyze the central evaluation questions of the prototype developed in the Relax project in terms of its efficacy in reducing stress in the workplace, different models will be constructed. First, the difference between the groups and thus the degree of individualization by the app will be determined. Second, the pre-post design will be used to ascertain whether the individuals exhibited a reduction in stress over time. These 2 approaches will use all stress-relevant outcomes to make assertions about the work stress of the individuals, namely the emotional states, self-reports on chronic stress as well as distress and eustress, and the physiological parameters. Linear mixed models will be used for the effectiveness analyses.

To address the usability and feasibility of the prototype, the data obtained from the satisfaction and usability scales will be used. These will also be analyzed between the groups and in the pre-post design. Exploratory analyses will test the secondary outcomes for possible effects. Additional moderation and mediation analyses will be possible here, in which the variables from the demographic and profile surveys could also be used. It is anticipated that the qualitative data from the user feedback will provide information about the specific background of the participants’ usability ratings.

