### Research Questions

This study aims to evaluate the prototype developed to date. The central research question of this evaluation is the effectiveness of the prototype in terms of the amount of stress reduction achieved by the participants. It is hypothesized that the greater the degree of personalization offered, the greater the reduction in stress. In addition, it was expected that all individuals would more or less experience an overall reduction in stress as a result of using the prototype. In addition to effectiveness, questions of usability and feasibility were addressed because of the pilot nature of the project approach and the research stage of the prototype at the time of the study. No hypotheses were formulated here, as the corresponding data were collected for exploratory purposes.

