### Ethical Considerations

The study design and conditions were initially approved in advance by the Ethics Committee of the University of Salzburg (EK-GZ 25/2023). Following minor alterations to the study design, including adjustments to the study duration, study period, the exclusion of a second sensor, and the reduction of the number of participants, an amendment was approved by the same committee (EK-GZ 25/2023 amendment). After data collection, a preregistration for hypothesis testing was performed (osf.io/myrd9). Due to the unpredictable nature of the study and the technical adjustments required during implementation, prospective preregistration was not performed.

Before completing the screening questionnaire, respondents were informed of the purpose of the data collection in order to provide informed consent. Those who were screened positively were informed of the acceptance of their registration via the email address they had provided. Those who were screened negatively were informed of the exclusion immediately after the screening. After the conclusion of the registration period, the final registration confirmations were sent out to all individuals included in the optimally balanced sample. Subsequently, the positions of those who had dropped out before the commencement of the study were filled by new participants until shortly before the study began. The identities of the participants were pseudonymized before the collection of study data. Participants were provided with an individual, reproducible code comprising questions on personal characteristics that could not be traced back [51]. The identity was only traceable by means of a coding list, which was kept by the study management and was only consulted in serious technical cases, dropouts or when checking whether the level of participation was sufficient to apply for the proposed compensation. Interested individuals were informed about the financial compensation worth €180 (US $204.86) (including the value in kind of retaining the study sensor). They could opt out at any point without negative consequences.

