### Sample Size

The optimal sample size for the central analysis of main effects was calculated using an a priori power analysis with G*Power (version 3.1) [52]. With an α value of .05, a power of 1-β=0.80, and a desired effect size of Cohen *d*=0.5, this resulted in a recommended sample size of 31. The sample size was increased in the study to the maximum number of participants that could be financed, which was 50 individuals. This resulted in a maximum of 25 (50%) individuals per experimental group.

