**Primary**											
	Momentary emotional state	Arousal, valence		Daily EMA^a^ (morning, interval)		Internally created scale		7-point Likert scale		“My current mood is:”	
	Emotional state of last stress event	Arousal, valence		Daily EMA (interval)		Internally created scale		7-point Likert scale		“My mood was:”	
	Chronic stress	Lack of satisfaction, high demand, loss of control, ability to recover, and negative emotions		Daily EMA (interval)		Selected items from CSSS^b^ [53] and LKCS^c^ [54]		7-point Likert scale		“I couldn’t relax today.”	
	Work-related distress	Relationship, personal accountability, work-life balance, and workload		Pre-post online		VEDAS^d^ [55], online		6-point Likert scale		“Dealing with ambiguous or ‘delicate’ situations.”^e^	
	Work-related eustress	Relationship, personal accountability, work-life-balance, and workload		Pre-post online		VEDAS [55], online		6-point Likert scale		“Dealing with ambiguous or ‘delicate’ situations.”^e^	
	Satisfaction	Overall satisfaction, workday adaptability, exertion due to EMA, and exertion due to sensor handling		Pre-post online		CSAT^f^ [56], internally extended), online		5-point Likert scale		“How would you rate your overall satisfaction with Relax?”	
	Usability	—		Pre-post online		SUS^g^ [57], online		5-point Likert scale		“I found using the Relax app unnecessarily complicated.”	
	HRV^h^	SDRR^i^, RMSDD^j^, and LF^k^/HF^l^		Continuously		Polar VS^m^		Passive		—^n^	

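### Eight outcomes are labelled primary with no lead outcome or success rule, two of them belong to a part called exploratory elsewhere, and the single-test alpha of .05 does not describe at least 12 stress tests

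*Protocol article*

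**What the plan says.** Table 1 lists eight outcomes under the heading Primary: momentary emotional state, emotional state at the last stress event, daily chronic stress, work-related distress, work-related eustress, satisfaction, usability and heart rate variability. The Primary Outcomes section goes through them in four numbered groups without ranking them.

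The Statistical Analysis section poses two effectiveness questions, the difference between groups and the pre-post change. It then states: "These 2 approaches will use all stress-relevant outcomes to make assertions about the work stress of the individuals". The outcomes it goes on to name are six of the eight. Satisfaction and usability receive the same two comparisons in the next paragraph.

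A significance level appears only under Sample Size, which begins "The optimal sample size for the central analysis of main effects was calculated using an a priori power analysis" and gives as inputs "With an α value of .05, a power of 1-β=0.80" and "a desired effect size of Cohen *d*=0.5". It names neither the outcome nor the test.

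On usability and feasibility, the Research Questions section says "No hypotheses were formulated here, as the corresponding data were collected for exploratory purposes", and the Abstract also calls the usability analyses exploratory. Yet Table 1 lists satisfaction (sample item: "How would you rate your overall satisfaction with Relax") and the System Usability Scale (SUS) as primary. The Primary Outcomes section does the same, and the Secondary Outcomes section describes the quantitative satisfaction survey as a primary measure.

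On timing, Ethical Considerations reports: "After data collection, a preregistration for hypothesis testing was performed".

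**The concern.** The article states two directional hypotheses: more personalization gives a larger stress reduction, and everyone improves to some degree. It does not say which outcome decides either one, or how many of the six must agree. A mixed pattern of results could then be read as support or as no support, depending on which outcome is put first. The .05 used for sample size covers one test, so it cannot be quoted as the error rate of the whole effectiveness analysis.

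The label conflict matters separately. If satisfaction and usability are primary, they carry confirmatory weight without a hypothesis. If they are exploratory, they should not sit in the primary block. Registration after data collection also means that the registration date cannot show that outcome emphasis was fixed before the data existed.

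**Working it through.** **1. Counting outcomes and scores (Table 1).**

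| Primary outcome | Scores | Named for effectiveness |
|---|---|---|
| Momentary emotional state | 2 | yes |
| Emotional state, last stress event | 2 | yes |
| Chronic stress (daily) | 5 | yes |
| Work-related distress | 4 | yes |
| Work-related eustress | 4 | yes |
| Heart rate variability | 3 | yes |
| Satisfaction | 4 | no |
| Usability (taken as one score) | 1 | no |

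Stress outcomes: 6, with 2+2+5+4+4+3 = 20 scores. All primary outcomes: 8, with 20+4+1 = 25 scores. With two questions, the stress family has 6 × 2 = 12 tests at outcome level and 20 × 2 = 40 at score level.

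**2. Reproducing the plan's own figure.** The stated sample size is 31. The normal formula for one within-person test, two-sided, gives n = ((z₀.₉₇₅ + z₀.₈₀)/d)² = ((1.960 + 0.842)/0.5)² = 31.4. So 31 fits a single within-person test at .05. The exact paired t-test gives 34 two-sided and 27 one-sided. Nothing in the calculation allows for more than one test.

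**3. Family-wise error.** Assumptions: each test is run at .05 two-sided without adjustment, and one success is enough. For k independent tests the chance of at least one false positive is 1 − 0.95^k. For correlated outcomes, equicorrelated normal statistics were simulated with assumed correlations of 0.3, 0.5 and 0.7, treating the two questions as independent of each other. The documents give no correlations.

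| Family | Tests | Independent | 0.3 | 0.5 | 0.7 |
|---|---|---|---|---|---|
| 6 stress outcomes × 2 | 12 | 0.46 | 0.43 | 0.37 | 0.30 |
| 8 primary outcomes × 2 | 16 | 0.56 | 0.51 | 0.44 | 0.35 |
| 20 stress scores × 2 | 40 | 0.87 | 0.79 | 0.66 | 0.49 |

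**4. Favourable errors only.** The hypotheses are directional, so a false claim of benefit has probability .025 per two-sided .05 test. For 12 independent tests: 1 − 0.975¹² = 0.26. The simulation gives about 0.20 at correlation 0.5. For 40 tests: 1 − 0.975⁴⁰ = 0.64 if independent, about 0.38 at correlation 0.5.

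**5. What naming one outcome preserves.** For d = 0.5 and N = 46, a paired t-test at .05 has power 0.91. Bonferroni over 12 tests (.05/12 = .0042) lowers it to 0.65. For the between-group question, assuming 23 per arm (the split is not given) and a two-sample t-test without baseline adjustment, power is 0.38 at .05 and 0.11 at .0042.

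**The case against.** The strongest reply is that the article nowhere says each outcome, still less each subscale score, is tested at .05. It names groups of outcomes and linear mixed models and gives no testing level. Nor does it say that one success is enough; if all six had to agree, the false-positive rate would not be inflated. Both points stand, so the error rates above are conditional and do not describe a stated plan.

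A reader might infer that 25 scores are each tested at .05, or that a spurious significant result is more likely than not. The documents do not support either reading. The effectiveness sentence covers six outcomes, and the 12-test family stays below 50% even with independence. Counting only favourable errors, it is about 26% or less. A chance above one half arises only under wider counts: 16 tests that are independent or weakly correlated, or score-level testing, and the latter not at every correlation.

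A reader might also infer that no adjustment is planned. A registered plan exists and is not shown, and an adjustment method is often left to such a document, so its absence here is no finding. Late registration is disclosed, and the article says the analyses are still to be carried out, so a plan fixed before analysis can still limit selective emphasis.

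Finally, the article calls the study a pilot, claims only preliminary effectiveness and calls for a controlled follow-up. That lowers the cost of a false positive. It does not remove the problem, because effectiveness hypotheses are stated and testing them is planned. Choosing the primary outcomes and labelling usability are decisions that the protocol itself makes, and no separate analysis plan cures the contradiction between its sections.

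**Conclusion.** The point holds as a matter of unranked primary outcomes and inconsistent labels. Eight outcomes are called primary with no lead outcome, hierarchy or success rule. Two effectiveness questions are put to six of them, giving at least 12 tests, while the .05 belongs to one unnamed main-effects test.

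If that level is used unadjusted and any one success counts, the chance of at least one false positive is about 46% with independence and about 30% to 43% at correlations of 0.7 to 0.3. It is higher at score level. The correlations, the unadjusted level and the any-success rule are all assumptions. Separately, and without any assumption, satisfaction and usability are primary in Table 1 and the outcome sections, while the Abstract and Research Questions treat usability as exploratory and without hypotheses.

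Should-fix, moderate confidence, given the pilot status and the registered plan that is not at hand.

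**What to change.** Before any outcome data are examined:

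- **Name one stress outcome as primary for both hypotheses.** One candidate is the mean of the work-related distress scale of the Valencia Eustress-Distress Appraisal Scale (VEDAS). The article does not define a distress score across the four subscales, so it would have to be written down. Table 2 schedules this scale at T1, T2 and T3, but the Primary Outcomes section mentions only the assessments after P1 and P2; reconcile these first, because a pre-post test from T1 depends on it.
- **State a fixed order for the two hypotheses.** The order matters: if the group question comes first and fails, which is likely at the power shown above, the pre-post test can no longer be claimed as confirmatory.
- **Make the other stress outcomes secondary**, either with Holm adjustment or as estimates with confidence intervals only.
- **Reconcile the label of satisfaction and the SUS** with the Abstract and Research Questions. Moving them to exploratory is the simplest way.

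Doing this only before group codes are opened is not enough, because the pre-post question needs no group codes. The amended plan should also record which data the team had already seen, since P1 sensor and questionnaire data were used in the break to train the stress-detection models.

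The cost is a paragraph in the registered plan and some relabelled rows in Table 1. The downside is that significance on the remaining outcomes can no longer be claimed unadjusted.

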## Methods

### Study Design

The study used a 2-arm randomized controlled design, comprising 2 experimental groups with varying levels of intervention. In a field design, participants applied the intervention in their natural (occupational) environment. Two 3-week study periods were conducted, with all participants receiving the same intervention in the first 3-week phase (P1) and, after a 3-week break, being allocated to 1 of 2 groups in the second 3-week phase (P2). This resulted in a within-subject comparison in the pre-post design as well as between-subject comparisons between both experimental groups. The within-subject design consisted of the collection of time series data enabled by the continuous daily measurement of variables. Subjective data on experiences and stress levels were collected daily in the morning and evening, as well as at least twice during the day, via the app. Continuous physiological data were also collected via wearing a sensor. In contrast, the between-subject design comprised 3 measurement points: before P1 (T1), between P1 and P2 (T2), and after P2 (T3). At these times, web-based questionnaires about chronic stress and various usability aspects of the wearable app system were submitted via a web-based survey platform. The break was used to improve the mobile app based on user feedback, split the participants into the experimental groups, train the models for automated stress detection based on the HRV and questionnaire data recorded in P1, and implement the weight adjustment mechanisms for personalized intervention delivery.

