The level of individualization of interventions in the respective experimental group was characterized by a variation in automatic individualization with regard to the interventions offered by the learning agent. Due to intentionally high α values during the adjustment of the intervention weight matrix, the *local* group had the possibility of significantly influencing their intervention delivery within 3 weeks, while the group *global* would only perceive minor changes. α-local describes the extent to which a rating changed the weight of an intervention for a single user. For the group *global*, it was set to 1.0 (no change to the user’s own weight), and for the group *local*, it was set to 2.1. The weights were adapted using the following formula: new_weight=old_weight * (alpha_local^old_weight). α-global describes the extent to which a rating changed the weight of an intervention for all users. It was set to 21 for both groups. The weights were adapted using the following formula: new_weight=old_weight *(alpha_global^(old_weight/number_of_users)).

Data entry was continuously monitored by the study team throughout the weeks. Participants were encouraged to continue their engagement through regular emails from the study team. It was expected that a general increase in adherence would be achieved as these messages were sent to all participants equally. If technical problems occurred, they were addressed individually via the app and generally via email. It is assumed that such individual correspondences would not add to the overall bias of the user experience since the individual disruption was already a bias, which is not uncommon in pilot studies. In P1, an update of the app was offered in the second week, which solved the technical problems that had arisen up to that point. Participants were given support to reinstall the app, and a self-help guide for the most common technical problems was offered. During the break between P1 and P2, additional technical difficulties were overcome by the study team, and when feasible and relevant, the participants’ input thus far was considered. Following this adaptation of the system in accordance with feedback, a graphical overview of the sensor data was made available in P2. This enabled the participants to maintain awareness of the data and its evolution over time.

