**Assessments**							
	VEDAS^g^		✓		✓		✓
	HRV^h^			✓		✓	
	Profile			✓			
	EMA^i^ (morning, interval, and evening)			✓		✓	
	CSAT^j^, SUS^k^, PSM^l^, and feedback				✓		✓

^a^T0: baseline.

^b^T1: before P1.

^c^P1: first 3-week phase.

^d^T2: between P1 and P2.

^e^P2: second 3-week phase.

^f^T3: after P2.

^g^VEDAS: Valencia Eustress-Distress Appraisal Scale.

^h^HRV: heart rate variability.

^i^EMA: ecological momentary assessment.

^j^CSAT: customer satisfaction score. The CSAT was expanded with 3 additional items.

^k^SUS: System Usability Scale.

^l^PSM: price sensitivity meter.

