Third, the level of satisfaction was assessed using the web-based questionnaire administered after P1 and P2. In this instance, the customer satisfaction score [56] was expanded with 3 supplementary items that were specifically designed to assess satisfaction and effort with the Relax approach. The items included ratings for overall satisfaction, workday adaptability, exertion due to EMA, and exertion due to sensor handling. The participants were required to indicate their level of agreement with the statements on a 5-point Likert scale.

Fourth, the System Usability Scale [57] was used to assess usability in the web-based questionnaire at P1 and P2. The items that were specifically reformulated for the Relax approach were collected using a 5-point Likert scale.

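### Satisfaction and usability are assigned a pre-post analysis but are rated only at T2 and T3, both after use and with app changes for everyone in between, so their time effect is not a pre-post effect of the prototype

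*Protocol article*

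**What the plan says.** Table 1 lists satisfaction (the customer satisfaction score with three added items) and usability (the System Usability Scale) among the primary outcomes. It gives the measurement design of both as "Pre-post online". After describing the effectiveness models, the Statistical Analysis section turns to these two scales: "These will also be analyzed between the groups and in the pre-post design".

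On timing, the Primary Outcomes section says that "the level of satisfaction was assessed using the web-based questionnaire administered after P1 and P2", and that "the System Usability Scale [57] was used to assess usability in the web-based questionnaire at P1 and P2". Table 2 agrees: its row for satisfaction, usability, price and feedback is ticked at T2 and T3 only. The work-stress questionnaire (VEDAS) is ticked at T1, T2 and T3.

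On what happened between T2 and T3, the Study Design section says: "The break was used to improve the mobile app based on user feedback". The App Intervention section adds that further technical difficulties were resolved in the break and that "a graphical overview of the sensor data was made available in P2".

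**The concern.** A pre-post analysis needs a value taken before exposure. For stress, the same section uses the term for change over time under the intervention, and Table 2 gives VEDAS a T1 value to support that. Satisfaction and usability have no such value. Their only within-person contrast runs from one post-use rating to another, and these scales rate the software itself, which was altered in the interval. A reader who takes the label at face value would treat an average rise from T2 to T3 as something the prototype achieved. It may instead reflect fault repair, the new display, familiarity or the passage of time. This matters because the Discussion expects feasibility and usability to dominate the results.

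**Working it through.** The document states no figure that bears on this point, so the check is a comparison of sections followed by an identification argument.

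**1. Ratings before and after first use (Table 2)**

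| Scale | Before first use | After first use |
|---|---|---|
| VEDAS | 1 (T1) | 2 (T2, T3) |
| Satisfaction | 0 | 2 (T2, T3) |
| System Usability Scale | 0 | 2 (T2, T3) |

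One sentence in Study Design could be read as placing usability items at all three survey points. It covers the stress and usability surveys together. Table 2 and the Primary Outcomes text are specific to each scale and do not support a T1 usability rating.

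**2. What differs between T2 and T3 for every participant**

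- App improvements from user feedback and further technical fixes (Study Design, App Intervention).
- A sensor-data overview, provided in P2 (App Intervention).
- Selection weights re-set after P1 from all users' interactions, and weight adaptation in operation during P2 (App Intervention).
- Interval-questionnaire reminders raised from 2 to 3 per day (App Intervention).
- Another three-week phase of use, and later calendar time.

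All participants had to start and complete the phases together (App Intervention), so no staggered start separates these elements from time.

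**3. What is not shared**

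Adaptation to a user's own ratings is the randomized factor. The local alpha is 1.0 in the global group, meaning no change to the user's own weight, and 2.1 in the local group. The global alpha is 21 in both.

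**4. What the two ratings can identify**

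Write the mean T2-to-T3 change in arm g as

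D(g) = A + R + W + P + C + G(g)

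where A is the app changes and new display, R the extra reminder, W the shared weight re-set and adaptation, P practice, C calendar time, and G(g) the arm-specific part.

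- The time main effect is the average of D(local) and D(global), which equals A + R + W + P + C plus the mean of the two G terms. This is one quantity containing five shared components, and with one rating per phase no model can separate them.
- The group contrast is D(local) − D(global) = G(local) − G(global). The five shared terms cancel. Without the additive form it remains a randomized comparison under P2 conditions.

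**5. Is T2 a valid baseline for the group contrast?**

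T2 lies between P1 and P2, so it precedes exposure to the arm-specific weighting, and participants were not told their allocation. The T2 score can therefore serve as a covariate.

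**The case against.** The best defence is that pre-post is shorthand here. Table 1 uses the same label for open-text feedback and acceptable price, which also cannot sensibly be rated before use, so it may simply mark the repeated web survey as opposed to the daily entries. The true timing is disclosed, T2 does precede the randomized phase, and no hypotheses are formulated for usability. The Limitations acknowledge that planned and unplanned technical adjustments can affect the data, and that there is no untreated control. A T2 covariate is also the kind of modelling detail often left to an analysis plan.

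Much of this stands, and it limits the severity. It does not remove the point. The label sits beside a stress analysis in which pre-post has its usual meaning. The technical caveat is illustrated by missing recordings, transmission errors and distorted stress data, and the control-group caveat concerns stress effects. Neither says how a T2-to-T3 change in these two scales may be read.

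A reader might infer more than the documents support:

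- *That the group comparison is also compromised.* It is not, because the updates were shared by both arms.
- *That the plan credits personalization with the change over time.* It ties the degree of individualization to the difference between groups.
- *That T2 to T3 compares one app version with the next.* An update was already offered in the second week of P1, and practice, reminders and calendar time also differ, so it is not a clean version comparison.
- *That a T1 rating should have been taken.* A usability rating before any use has no meaning.

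**Conclusion.** The concern holds in limited form. The stated pre-post analysis of satisfaction and usability conflicts with the document's own schedule. The T2-to-T3 time main effect combines at least five influences common to both arms and cannot be read as a pre-post effect of the prototype. The local-versus-global contrast stands.

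The severity is minor to moderate: both scales are listed as primary, but the questions they serve are exploratory. No numerical size is given, because the documents contain no estimate of how far fixes or familiarity would move either scale. The conclusion rests on two readings: that Table 2 and the Primary Outcomes text give the actual rating times, and that the T2 survey was completed before P2 began.

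**What to change.** - In Table 1 and the Statistical Analysis section, replace pre-post with post-P1 versus post-P2 for these two scales.
- Make the inferential analysis the local-versus-global comparison at T3, with the participant's own T2 score as covariate. This uses data already collected and gains precision to the extent that T2 and T3 scores are correlated.
- Report T3 levels as the usability and satisfaction result for the current prototype.
- Report T2-to-T3 change descriptively, alongside the open-text feedback. State that it mixes app changes, practice, reminders, the start of weight adaptation and calendar time, and that it is not a clean version comparison.

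The Results section says the analyses are still to be carried out, so this needs only changes of wording and one model specification. The price is one exploratory significance test, that of the time effect on these two scales.
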